### Who will take informed consent? {26a}

Patients with RA and PsA that suffer from wrist arthritis will be screened for eligibility by their treating rheumatologist in the outpatient clinic of the Maasstad Hospital. If they meet the inclusion and exclusion criteria, they will receive the study information and will be given a minimum of 72 h to consider participation. Patients from referring hospitals (EMC, FGV, LUMC, ASH) will be pre-screened and notified about the study by their treating rheumatologist. If subjects are interested, they will receive study information and be referred to the Maasstad Hospital for full screening and briefing. Informed consent will be signed together with a study-trained member of the research team, which is either a rheumatologist, physician or physician assistant.

### Additional consent provisions for collection and use of participant data and biological specimens {26b}

All patients randomized for arthroscopic synovectomy of the wrist will be asked to participate in a separate study regarding the disease profiling of RA and PsA for which arthroscopically removed synovial tissue will be stored for later analysis (see the ‘Plans for collection, laboratory evaluation and storage of biological specimens for genetic or molecular analysis in this trial/future use {33}’ section). For the same purpose, patients from both groups will be asked for the collection of additional blood specimens. No additional study procedures are required for this ancillary study. The decision to participate in this ancillary study is optional and has no consequences for participation in the ARCTIC trial.

## Interventions

### Explanation for the choice of comparators {6b}

Both comparators, arthroscopic synovectomy and IACSI of the wrist, are part of the standard of care for patients with inflammatory wrist arthritis in the Maasstad Hospital. Wrist arthroscopy is a minimally invasive procedure that has been adopted by many hand and wrist experts to treat various wrist pathologies. Despite earlier studies demonstrating good outcomes of arthroscopic synovectomy in the rheumatic wrist, it is not regularly used for this indication. IACSI are administered commonly by rheumatologists, orthopaedic surgeons and primary care physicians for the treatment of inflammatory arthritis and osteoarthritis worldwide. In cases of therapy-refractory inflammatory arthritis of specific joints, they are considered the first-choice treatment. Therefore, IACSI was chosen as the comparator in this study. Despite the evidence that only 66% of palpation-guided IACSI are injected accurately, compared to 83% of ultrasound-guided IACSI [22], ultrasound-guided injections were not chosen for this study because we felt it did not represent regular clinical practice, where palpation-guided injection is still the norm.

### Intervention description {11a}

#### Arthroscopic synovectomy

Wrist arthroscopies will be performed in the Maasstad Hospital or in the Spijkenisse Medical Centre, which is a nearby collaborating hospital. All arthroscopies will be performed by one hand and wrist surgeon with a high level of experience, based on a scale introduced by Tang and Giddins [23]. Arthroscopies will be performed in day surgery according to international standards. No antibiotic prophylaxis will be given. Patients will undergo general anaesthesia or brachial plexus block. All interventions will be performed under tourniquet exsanguination. The forearm will be positioned upright and in a neutral position with the elbow flexed by 90°. Axial traction of 4–6 kg will be applied. Four entrees are created on the dorsal side of the wrist by superficial incisions followed by insertion of a blunt tool through the joint capsule. There are two radiocarpal entrees, between the third and fourth extensor tendon compartment [3, 4] and radially of the sixth extensor tendon compartment (6R), and two midcarpal entrees, on the ulnar (MCU) and radial (MCR) side (Fig. 1). The joint is visualized using a 2.7-mm arthroscope with 30° angulation. The camera and instruments can be switched between the entrees to optimize visibility and instrumental reach. The location and extent of synovitis will be clearly documented. Cartilage damage will be graded using the Outerbridge classification system [24]. Scapholunate and lunotriquetral ligament injuries will be classified according to Geissler [25]. Triangular fibrocartilage complex injuries will be classified according to Palmer [26]. These injuries will be documented and managed based on the surgeon’s expertise. A shaver is used for the removal of synovitis, mucoid dysplasia and cartilaginous debris. Irrigation fluid is passed through a filter to collect synovial tissue samples, to be stored for later analysis. Finally, 40 mg of triamcinolonacetonide (Kenacort-A) will be deposited in the wrist joint. The portals will be closed with sterile adhesive tape or single nylon sutures. A soft pressure dressing will be applied for 48 h. The procedure will take approximately 60 min in total. Patients will be instructed to mobilize the wrist immediately. Wound inspection will be performed 10 to 14 days after surgery.

**Fig. 1 Fig1:**
[figure not shown]
Wrist arthroscopy portals. Abbreviations: 3–4 portal between the third and fourth extensor tendon compartments, 6R portal radial of the sixth extensor tendon compartment, MC-R midcarpal radial portal, MC-U midcarpal ulnar portal

#### Intra-articular corticosteroid injections (IACSI)

Forty milligrammes of triamcinolonacetonide (1 ml of 40 mg/ml Kenacort-A) will be injected into the joint under palpation guidance using a 21G (green) needle or 23G (blue) needle. A pressure dressing will be applied for 8 h. Patients can start exercising the wrist immediately. The procedure will take approximately 5 min.

### Criteria for discontinuing or modifying allocated interventions {11b}

Patients may leave the study at any time for any reason if they wish to without any consequences. The investigator can decide to withdraw a subject from the study for urgent medical reasons. All patient data collected before withdrawal from the study can still be included in the analysis. Subsequent treatment to the wrist can be given as usual after the primary endpoint 3 months after the intervention. This also means patients are allowed to receive the intervention of the other study group. These cross-over patients will be accounted for in the per-protocol analysis.

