### Strategies to improve adherence to interventions {11c}

All study visits are planned simultaneously with the routine visits with the rheumatologist to minimize patient burden and improve study adherence. Patients will be contacted by telephone 2, 4 and 6 weeks after the intervention to obtain pain scores and to answer questions from the patient. All study questionnaires can be completed digitally within a 14-day timeframe. A reminder will be sent after 10 days.

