### Relevant concomitant care permitted or prohibited during the trial {11d}

Systemic anti-rheumatic therapy (i.e. DMARDs and systemic corticosteroids) will be discontinued 2 weeks before intervention and restarted directly after the intervention to ensure wash-out of medication for the purpose of synovial biopsy and blood sample analysis. Based on long-term experience, brief discontinuation of systemic medication will not trigger a flare of disease activity. Patients undergoing IACSI will also stop anti-rheumatic therapy 2 weeks in advance to avoid treatment bias. Analgesics (including NSAIDs) do not have to be discontinued. To accurately measure the treatment effect of the interventions, anti-rheumatic medication (i.e. DMARD therapy and systemic corticosteroids) cannot be adjusted during the first 3 months after the intervention. Three months is the primary endpoint and the regular timeframe for evaluating the effect of anti-rheumatic therapy in rheumatology practice. Exceptions are made if patients suffer from severe or acute symptoms, determined by the treating rheumatologist. Adjustments to analgesics and anti-rheumatic therapy after 3 months are permitted but will be recorded.

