### Outcomes {12}

#### Primary outcome

The primary outcome is the difference in wrist function, measured with the Patient-Rated Wrist Evaluation (PRWE) at 3 months compared to baseline. The PRWE is a measure of pain and wrist function in activities of daily living. The PRWE will be measured as a secondary outcome at 6 and 12 months.

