## Statistical methods

### Statistical methods for primary and secondary outcomes {20a}

The primary analysis will be performed according to the intention-to-treat principle. A per-protocol analysis will also be conducted accounting for possible cross-over patients. A description of the planned intention-to-treat and per-protocol analyses for outcome PRWE conform to the estimands framework is provided as a supplementary file [42, 43]. Baseline patient characteristics will be analysed using simple descriptive statistics. Differences in the change in the primary outcome (PRWE at 3 months minus PRWE at baseline) between the two groups will be analysed using a linear mixed model, including the baseline measurement in the outcome vector and stratification variable disease (RA/PSA), time and treatment × time interaction as covariates. The difference in the change in PRWE score will be considered statistically significant if *p* < 0.05 (likelihood ratio test). The model will be extended by including the other time points to assess further trends in the development of PRWE scores. The secondary outcomes, EULAR response rate, DAS28 scores, EQ-5D-5L scores, range of motion (ROM), grip strength and pain (NRS) will be analysed in a similar manner. Differences between the two treatment groups in rates of complications and secondary interventions will be analysed using Pearson’s chi-square test or Fisher’s exact test. IBM SPSS (version 23.0, Chicago, IL) or similar software will be used for analysis.

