### Methods in analysis to handle protocol non-adherence and any statistical methods to handle missing data {20c}

Loss to follow-up will be minimized by the adherence strategies described above. The sample size is calculated to cope with a loss to follow-up of 5% and still enable enough statistical power. Furthermore, the use of a linear mixed model will allow to retain patients with missing follow-up measurements in the analysis and obtain unbiased estimates under the missing at random (MAR) assumption.

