### Adverse event reporting and harms {22}

Adverse events reported by the patient or observed by the investigators during follow-up will be documented in the medical record and the eCRF. Complications of wrist arthroscopy include those related to anaesthesia, neuropraxia, wound infection, haematoma, painful scar tissue and damage to cartilage and tendons. Complications of IACSI include site infection, haemorrhage, pain and skin hyper- or depigmentation. Serious adverse events (SAEs) will be reported to the Central Committee on Research Involving Human Subjects (CCMO) as required by law.

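### Investigator-led withdrawal for urgent medical reasons is worded as leaving the study, so it can end outcome collection when only treatment decisions need to change; a cheap wording fix

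*Protocol article*

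**What the plan says.** The rule stands in the protocol article under Criteria for discontinuing or modifying allocated interventions {11b}. Apart from the patient's own right to leave, it gives one investigator-led route: "The investigator can decide to withdraw a subject from the study for urgent medical reasons". The next sentence reads: "All patient data collected before withdrawal from the study can still be included in the analysis". The article does not say whether anything is collected afterwards.

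Other sections bear on this:

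- **Primary outcome:** wrist function is "measured with the Patient-Rated Wrist Evaluation (PRWE) at 3 months compared to baseline". Table 1 schedules the PRWE at baseline and months 3, 6 and 12 only.
- **Analysis {20a}:** "The primary analysis will be performed according to the intention-to-treat principle".
- **Missing data {20c}:** the linear mixed model is relied on to "obtain unbiased estimates under the missing at random (MAR) assumption".
- **Harms {22}:** "Adverse events reported by the patient or observed by the investigators during follow-up will be documented in the medical record and the eCRF". Table 1 schedules complications and secondary treatment at weeks 2, 4 and 6 and months 3, 6 and 12.
- **Concomitant care {11d}:** anti-rheumatic medication is held fixed for the first 3 months, but "Exceptions are made if patients suffer from severe or acute symptoms, determined by the treating rheumatologist".
- **Adherence {11c}:** "All study visits are planned simultaneously with the routine visits with the rheumatologist", and the questionnaires are digital.
- **Blinding {17a}:** patients, researchers, rheumatologists and surgeons all know the allocation.

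**The concern.** The section heading is about interventions, but the rule is about the study. Each arm receives one procedure: an arthroscopy with corticosteroid deposition, or one injection. After that there is no continuing trial treatment to stop, so withdrawing the patient mainly removes later measurements. It is not needed in order to treat the patient, because {11d} already allows medication to change early for severe or acute symptoms with the patient still in the trial.

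The decision lies with someone who knows the allocation, and urgent medical reasons are not defined. Some of those reasons may be a poor result in the study wrist. In that case the 3-month PRWE goes missing because of what it would have shown, and the model fills the gap with a course that is too favourable. The arm with more such withdrawals would look better than it is. Trial-recorded follow-up of the event would also stop at withdrawal, although the abstract names safety among the things this trial will evaluate.

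**Working it through.** **1. The plan's own figure.** Sample size {14} gives a difference of 11.0, SD 15.0, baseline correlation 0.1, α = 0.05 (taken as two-sided), 90% power, 38 per arm, and 40 after a 5% loss.

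- With the baseline value in the outcome vector, the effective SD is 15 × √(1 − 0.1²) = 14.92.
- n per arm = 2 × (1.960 + 1.282)² × 14.92² / 11² ≈ 38.7, so 39. With SD 15 the result is 40.
- Power at 38 per arm is 0.895 by formula and about 0.89 in a 10,000-draw simulation with a likelihood ratio test.
- 38 / 0.95 = 40.

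The stated size is reproduced to within two patients and is not in dispute.

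**2. Does the loss matter for power?** The 5% allowance covers 0.05 × 40 = 2 patients per arm. With 1, 2 or 4 patients missing from one arm of 40, power is 0.906, 0.902 or 0.894, against 0.909 with none missing. It hardly moves, so the issue is bias.

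**3. What the primary model knows about a patient withdrawn before month 3.** Table 1 has no PRWE between baseline and month 3, so the patient contributes only the baseline value. At the assumed correlation of 0.1, baseline explains 0.1² = 1% of the variance at 3 months. A patient 15 points worse than average at baseline is expected to be only 0.1 × 15 = 1.5 points worse at 3 months. In effect the model gives the patient the arm's average course. Pain scores and complications are collected at weeks 2, 4 and 6 but are not in the stated primary model.

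**4. Size of the bias.** Let k patients in one arm of 40 be withdrawn before month 3, with an unseen PRWE that is d points worse than the model implies. The arm mean is then too favourable by k × d / 40. Both k and d are assumptions; the documents give neither.

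| k | d | Shift (points) | Share of 11 |
|---|---|---|---|
| 1 | 15 | 1 × 15 / 40 = 0.38 | 3.4% |
| 1 | 30 | 1 × 30 / 40 = 0.75 | 6.8% |
| 2 | 15 | 2 × 15 / 40 = 0.75 | 6.8% |
| 2 | 30 | 2 × 30 / 40 = 1.50 | 13.6% |
| 3 | 30 | 3 × 30 / 40 = 2.25 | 20.5% |

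This assumes that all such withdrawals fall in one arm. If both arms are affected alike, the shifts cancel in the difference.

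**5. A check against the article's own complication count.** The Background cites a systematic review with two complications in 153 wrists. That is 40 × 2 / 153 = 0.52 per arm of 40. If every one led to withdrawal before month 3, the shift would be 0.52 × 15 / 40 = 0.20 to 0.52 × 30 / 40 = 0.39 points, or about 2% to 4% of the target. The article rates those studies at high risk of bias, so the count may be low.

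**The case against.** The strongest reply has four parts.

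**The rule is a permission.** It does not define urgent reasons as harm from the procedure; they may be unrelated illness. Complications are listed as an outcome to record, and nothing names them as grounds for withdrawal. This stands. A reader might infer that the patients who were harmed will be dropped, but the text supports only that they can be.

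**Later collection is not forbidden, and other documents may settle it.** The sentence on earlier data does not exclude data gathered afterwards. The full protocol and the estimand supplement named in {20a} are not shown. This stands in part. The supplement may say how such patients are analysed, but no analysis recovers a PRWE that was never collected. If the full protocol already continues collection, the article's sentence only needs to be brought into line with it.

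**There is no contradiction with intention to treat or with missing at random.** Patients with missing outcomes stay in their randomised arm, and {20c} claims unbiasedness only under its stated condition. This stands. A reader might call the passages contradictory; the most that can be said is that the rule makes avoidable missing data of the kind that strains the condition.

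**The size is assumed.** This stands too. The 20% figure needs three early withdrawals, all in one arm, each 30 points worse.

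A further tempting step is to argue that cancelled anaesthesia would remove patients from the surgical arm alone between allocation and procedure. The article does describe anaesthesia only for that arm, but nowhere says that a cancelled procedure leads to withdrawal from the study, so the point is not pressed.

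**Conclusion.** The wording point holds and is modest. As written, {11b} lets an unblinded investigator end a patient's participation for urgent medical reasons and assures only the data gathered before that, although single-procedure interventions leave little treatment to stop. A withdrawal before month 3 loses the primary outcome, possibly for an outcome-related reason. A later one loses only the remaining visits. The triggering event can still be recorded and routine care goes on; what is cut short is the trial's own follow-up of complications.

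The likely bias is about 0.4 points per patient withdrawn at a 15-point deficit and about 2 points in an unfavourable case, against a target of 11. Both figures rest on assumed counts and deficits, and the article's cited complication count points to the lower end. The documents do not show that bias will occur, nor that the primary analysis is invalid. This is a cheap improvement.

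**What to change.** Amend {11b}, for data collection only. State that an investigator's decision for urgent medical reasons does not end data collection, and that the scheduled PRWE questionnaires and the recording of adverse events and complications continue to month 12 unless the patient withdraws consent for data collection. Check that the full protocol and the estimand supplement say the same. Clinical decisions on treatment are left as they are.

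The cost is a wording amendment through the ethics committee by the route described in {25}. No visits are added, since the questionnaires are digital and study visits coincide with routine ones. The downside is a little follow-up effort for a few patients.

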### Strategies to improve adherence to interventions {11c}

All study visits are planned simultaneously with the routine visits with the rheumatologist to minimize patient burden and improve study adherence. Patients will be contacted by telephone 2, 4 and 6 weeks after the intervention to obtain pain scores and to answer questions from the patient. All study questionnaires can be completed digitally within a 14-day timeframe. A reminder will be sent after 10 days.

### Relevant concomitant care permitted or prohibited during the trial {11d}

Systemic anti-rheumatic therapy (i.e. DMARDs and systemic corticosteroids) will be discontinued 2 weeks before intervention and restarted directly after the intervention to ensure wash-out of medication for the purpose of synovial biopsy and blood sample analysis. Based on long-term experience, brief discontinuation of systemic medication will not trigger a flare of disease activity. Patients undergoing IACSI will also stop anti-rheumatic therapy 2 weeks in advance to avoid treatment bias. Analgesics (including NSAIDs) do not have to be discontinued. To accurately measure the treatment effect of the interventions, anti-rheumatic medication (i.e. DMARD therapy and systemic corticosteroids) cannot be adjusted during the first 3 months after the intervention. Three months is the primary endpoint and the regular timeframe for evaluating the effect of anti-rheumatic therapy in rheumatology practice. Exceptions are made if patients suffer from severe or acute symptoms, determined by the treating rheumatologist. Adjustments to analgesics and anti-rheumatic therapy after 3 months are permitted but will be recorded.

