#### Secondary outcomes

The following secondary outcome measures will be measured at baseline, 3 months, 6 months and 12 months (Table 1):Range of motion (ROM) of the wrist measured using a standard goniometer, including pronation, supination, ulnar and radial deviation, and palmar and dorsal flexionGrip strength of the wrist measured using a dynamometer (Saehan). Grip strength will be calculated as the mean of three attemptsNumeric Rating Scale (NRS) pain scale. A score of 0 indicates no pain, and a score of 10 indicates the worst possible painEULAR response rate and Disease Activity Score (DAS28)Resolution of synovitis measured by wrist ultrasound in grey scale and power Doppler mode (baseline and 3 months only)Wrist arthritis and joint destruction on standard (plain) radiographs of the wrist (baseline and 12 months only)Quality of life measured with the EuroQol 5D (EQ-5D-5L) questionnaireBlood parameters including erythrocyte sedimentation rate (ESR) and C-reactive protein (CRP) (part of the routine clinical care)Complications and subsequent treatment

**Table 1 Tab1:** Trial schedule according to the recommendation for interventional trial (SPIRIT) guidelines

	Enrolment	Allocation	Post-allocation					
Timepoint**	*14 days (*± *4 days) prior to intervention*	Intervention	*Week 2*	*Week 4*	*Week 6*	*Month 3*	*Month 6*	*Month 12*
Enrolment								
Eligibility screen	X							
Informed consent	X							
Allocation	X							
Interventions								
Arthroscopic synovectomy		X						
Intra-articular corticosteroid injection		X						
Assessments								
Questionnaires (PRWE, EQ-5D-5L, iMCQ, iPCQ)	X					X	X	X
Physical exam (including ROM, GS and DAS28)	X					X	X	X
Wrist ultrasound	X					X		
Plain wrist radiographs	X							X
Blood parameters (ESR, CRP)	X					X	X	X
NRS pain scores	X		X	X	X	X	X	X
Complications and secondary treatment			X	X	X	X	X	X
Cost-effectiveness analysis								X

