### Composition of the data monitoring committee, its role and reporting structure {21a}

The need for a Data Safety Monitoring Board (DSMB) has been waived by the Medical Ethics Committee, because both study treatment modalities are considered low-risk and part of standard care.

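### No safety, pain or disease-activity assessment is scheduled during or at the end of the trial-imposed 2-week drug stop, so the statement that it causes no flare cannot be checked

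*Protocol article*

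**What the plan says.** Section {11d} of the protocol article states that systemic anti-rheumatic therapy (DMARDs and systemic corticosteroids) "will be discontinued 2 weeks before intervention and restarted directly after the intervention to ensure wash-out of medication", and gives the reason as "for the purpose of synovial biopsy and blood sample analysis". The injection arm is included: "Patients undergoing IACSI will also stop anti-rheumatic therapy 2 weeks in advance to avoid treatment bias". On the risk of this measure there is one sentence: "Based on long-term experience, brief discontinuation of systemic medication will not trigger a flare of disease activity".

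Table 1 (under Outcomes {12}) places enrolment, consent, allocation and baseline 14 ± 4 days before the intervention. Its row "Complications and secondary treatment" is blank at enrolment and at the intervention, and is marked at weeks 2, 4 and 6 and months 3, 6 and 12.

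The general rule is in section {22}: "Adverse events reported by the patient or observed by the investigators during follow-up will be documented in the medical record and the eCRF". The start of follow-up is not defined there, and the complications named are those of arthroscopy and of the injection. Section {21a} explains the absence of a data monitoring board "because both study treatment modalities are considered low-risk and part of standard care". Section {21b} gives a similar reason for having no interim analysis or stopping rule.

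**The concern.** The drug stop belongs to neither procedure. Its stated purpose is sampling, and sections {26b} and {33} describe the tissue and blood work as an optional separate study, analysed later. The reason given in {21a} and {21b} speaks of the two treatments and does not reach the stop. The patients concerned enter in an exacerbation that has not responded to at least 3 months of conventional DMARDs (section {10}).

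The article therefore makes a flat safety statement about a measure applied to everyone, while its schedule has no point at which that statement could be found wrong. The Discussion part of the Abstract names safety as something the trial evaluates. If flares or early restarts do occur, the report could not give their frequency, and a reader could not separate none occurred from nobody asked.

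**Working it through.** The plan gives no flare rate or other figure on this point, so there is none to reproduce. The check sets the schedule against the stop.

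**Inputs.** Stop: 14 days before the intervention, with restart directly after it ({11d}). Enrolment: 14 ± 4 days before the intervention (Table 1). Planned sample: 40 per arm, 80 in all ({14}).

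**Step 1: what is marked around the stop (Table 1).**

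| Assessment | Enrolment | Intervention | Next mark |
|---|---|---|---|
| Complications, further treatment | none | none | week 2 |
| NRS pain | yes | none | week 2 |
| DAS28 (physical exam) | yes | none | month 3 |
| ESR, CRP | yes | none | month 3 |

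No row has a mark between enrolment and week 2 except the interventions themselves.

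**Step 2: time from enrolment to the first marked complications contact.** Days from enrolment to intervention plus 14:
- shortest: 10 + 14 = 24 days
- nominal: 14 + 14 = 28 days
- longest: 18 + 14 = 32 days

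**Step 3: exposure.** 80 patients × 14 days = 1,120 patient-days off systemic therapy with no scheduled assessment at their end. This measures exposure, not harm.

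**Step 4: can later measurements stand in?** By week 2, systemic therapy has been restarted and both arms have received triamcinolone in the wrist ({11a}). A week-2 pain score, or a month-3 DAS28, mixes any flare during the stop with the restart and the intervention. Neither isolates what happened during the stop.

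**Step 5: are restarts recorded?** Section {11d} says explicitly that changes in therapy are recorded when they occur after 3 months. It gives no recording rule for a restart during the stop.

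**Step 6: does the stop fall within follow-up?** Section {22} does not say. The Abstract places follow-up at 3, 6 and 12 months, which suggests a start after the intervention but does not fix one.

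**Side check.** At the short end of the enrolment window (10 days), a 14-day stop would begin 14 − 10 = 4 days before enrolment and consent, or else be shorter than stated. Table 1 and {11d} need to be reconciled here too, because it affects whether recording from consent covers the whole stop.

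**The case against.** The strongest reply is that the marks in Table 1 are contact times, not reporting periods. A week-2 call can record something that happened earlier; otherwise a complication during surgery would also go unrecorded, since the intervention column is blank for it as well. Section {22} covers any event reported or observed, whatever its cause. Its lists of complications are introduced as examples, and serious events go to the competent committee without a stated start date. Section {11b} lets patients leave, or be withdrawn for urgent medical reasons, at any time. The arthroscopy arm also has a wound check 10 to 14 days after surgery ({11a}).

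This stands, and it rules out a stronger reading that a reader might infer: that complications are collected from week 2 only, so that harms of the stop lie outside the safety record. The documents do not say so. Exclusion of the stop is one reading of an undefined term, not a stated rule. Nor do the documents support a count of missed flares: they give no rate, and in patients already in an exacerbation a flare could not simply be attributed to the stop.

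A second reply is that an article may leave the start of adverse event recording to the full protocol (version 15, not shown). That weakens the point about the undefined start. It does not touch the visit schedule, which the article states in full and which has no assessment at the end of the stop. The flat no-flare sentence is likewise stated, not omitted.

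A third reply is that both arms stop for the same period, so the comparison is protected. This also stands: no bias in the PRWE comparison is shown.

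**Conclusion.** The point holds in a limited form. Every patient undergoes a trial-imposed drug stop whose safety is asserted without data, and the schedule has no complications, pain or disease-activity assessment during or at the end of it. Flares and early restarts in that window are not systematically captured, though spontaneous reports and serious events may be. The no-flare statement cannot be checked from the trial's data.

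The size is all 80 planned patients, about 14 days each, with 24 to 32 days from enrolment to the first marked complications contact. How many events this involves is unknown. The matter bears on the total harm of participation. Baseline PRWE, taken at enrolment, does precede any change during the stop, but that applies to both arms and gives no ground to expect a biased difference.

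The conclusion assumes that the marks in Table 1 are read in the right columns (six marks, six post-intervention time points) and that no unseen document adds an assessment at the intervention visit. It should be corrected, but it does not threaten the primary analysis.

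**What to change.** - In Table 1, mark complications and secondary treatment, and NRS pain, in the intervention column.
- At that visit, ask about flare and any restart of systemic drugs since the stop, and record both.
- In section {22}, state that adverse event recording runs from consent, and name flare during the stop among the events to be asked about.
- Report the frequency of flare and early restart, overall and by arm.
- In section {11d}, reword the no-flare sentence as an assumption that these data will check.

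Sections {11d}, Table 1 and {22} must be reconciled by the clinical team. This includes whether the exception for severe or acute symptoms in {11d} applies before the intervention. It follows the sentence on the first 3 months after the intervention but carries no time limit of its own. The fit of the 14 ± 4 day window with a 2-week stop needs settling as well. No clinical rule is proposed here.

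The cost is a few questions at a visit that every patient already attends, two table marks and short edits to two sections. The downside is a few more events to report.
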